#### Parallel-group RCT analysis

Using data from the first treatment period, we will compare those who received melatonin with those who received placebo based on intent-to-treat for all outcomes adjusted for the average baseline SOL determined by the pre-randomization sleep-hygiene phase. Outcomes measured daily will be analyzed both with time series methods and by using the outcome averaged across the treatment period. Outcomes measured weekly provide only one measurement per participant. Secondary analyses will examine effects defining treatment as that actually received.

#### Analysis of individual N-of-1 trials

At the end of each participant’s N-of-1 trial, a patient report will be forwarded to the referring physician in order to guide treatment decision. The patient report will present (1) the child’s SOL (according to parent diaries) for each day of the study; (2) the child’s mean and median SOL on both treatments; (3) whether the child’s SOL has normalized below 30 minutes; (4) whether the SOL is within the parent’s expectations of significant improvement; and (5) any reported adverse events. The patient and physician will make an individual decision about the continued use of melatonin.

#### Aggregated analysis

N-of-1 trials will be combined using a multilevel random effects model that incorporates variance within and between patients. This within-patient level will incorporate variation resulting from the treatment crossovers as well as time effects modeled in various forms (e.g., linear trends, nonlinear trends, and carryover effects). Each within-patient regression coefficient will be treated as a random effect that can vary based on these between-patient factors. The primary analysis will calculate the average treatment effect (i.e., will model the mean of the individual treatment effects as a constant). Secondary analyses will model the mean as a function of factors that vary among patients such as age, sex, and dose. These terms describe the main effects of these factors, their interactions with the treatment, and their interaction with time. A full list of the factors evaluated for these subgroup analyses is given below.

The full multilevel model will return estimates of both average effects across the population of patients, as well as effects for individuals informed by the results on other participants. The predicted effects for an individual are weighted averages of the individual’s data and the averages from others. This model incorporates correlations among the measurements within an individual. It also enables comparison of the individual’s predicted treatment effect using the multilevel model with that from using only that individual’s data.

Carryover, the phenomenon whereby the effects of one treatment may continue to affect the outcomes measured after the next treatment is started, is always a risk in crossover studies. It is not expected that placebo effects would carry over into a melatonin period, but melatonin effects may carry over into a placebo period. Carryover might also differentially affect measurements made in a melatonin treatment period that follows another melatonin treatment period. We will investigate various adjustments for carryover, such as discarding the first measurements in a treatment period on outcomes measured daily, to determine whether results are sensitive to carryover. These adjustments will allow for potential differential carryover by treatment regimen.

Bayesian models will be estimated using Markov chain Monte Carlo with model assessment using posterior predictive checks [48] and the deviance information criterion [49]. Non-Bayesian models will be fit using generalized linear and nonlinear mixed models.

#### Missing data

For the aggregated N-of-1 trial analysis, we will develop appropriate missing data models based on the data-missingness mechanism. We will first check if the data are missing completely at random and if not, as is likely, will adjust for observed variables related to missingness using, if possible, longitudinal fixed or random effects models, assuming the mean and covariance structures are known. If considerable data are missing on key predictors, we will use multiple imputation. As a sensitivity analysis, we will also analyze differences between groups at each time point imputing a change of zero for those missing follow-up.

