### Sample size

A proposed sample size was calculated for the parallel group RCT. The null hypothesis is that both group means are equal, and the alternative hypothesis is SOL will be 42 minutes on melatonin and 72 minutes on placebo [22]. To account for a potential dropout of 25 %, we assume that 25 % of the participants will show no effect of treatment and will therefore have a SOL of 72 minutes under both treatments. The average time in the treatment group will then be 49.5 minutes (as ¾ will have a time of 42, and ¼ a time of 72). The intent-to-treat effect will then be a 22.5-minute reduction in SOL. Assuming a pooled standard deviation of 60 minutes [22], randomization of 150 patients per group (300 total) will provide 90 % power with a type I error rate of 0.05 using a two-sided test. We will need to recruit 177 patients per group (354 total) to commence the sleep-hygiene phase in order to account for the 15 % of individuals expected to respond to sleep hygiene. Because the N-of-1 design will use multiple crossovers for each patient, this sample size will also achieve sufficient power for the aggregated N-of-1 analysis.

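### The stated missing-data sensitivity analysis, imputing zero change and comparing groups at each time point, is a poor check on the missing-at-random assumption

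*Protocol article*

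**What the plan says.** The Missing data section of the protocol article opens with the aggregated analysis: "For the aggregated N-of-1 trial analysis, we will develop appropriate missing data models based on the data-missingness mechanism". It expects that data will probably not be missing completely at random, and in that case the authors "will adjust for observed variables related to missingness using, if possible, longitudinal fixed or random effects models". Multiple imputation is conditional and concerns predictors: "If considerable data are missing on key predictors, we will use multiple imputation". One sensitivity analysis follows: "we will also analyze differences between groups at each time point imputing a change of zero for those missing follow-up". The text does not say what change is measured from, or how the uncertainty of the imputed values is handled.

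The analysis being checked is described under Aggregated analysis: "N-of-1 trials will be combined using a multilevel random effects model that incorporates variance within and between patients". The other sensitivity checks in the article concern the prior distributions and carryover, not missing data.

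The Sample size section sets the expected loss: "To account for a potential dropout of 25 %, we assume that 25 % of the participants will show no effect of treatment".

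**The concern.** The main approach adjusts for observed variables related to missingness. What remains untested is whether children left for reasons tied to their unobserved sleep onset latency (SOL). The protocol gives grounds to expect this: under Early stopping it lists perceived lack of effectiveness, dramatic improvement and safety concerns as the usual reasons for ending a period early, and under Withdrawal it allows children to leave for adverse events.

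A useful sensitivity analysis would hold the model fixed and vary what is assumed about the missing values. The stated rule does neither. It assumes one value, zero change, for every missing child and treats it as if observed. It also replaces the multilevel model with separate between-group comparisons. The risk is a check that looks conservative, because the estimate shrinks, and is reported as evidence of robustness when it has hardly tested the assumption.

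**Working it through.** **Inputs from Sample size.** "the alternative hypothesis is SOL will be 42 minutes on melatonin and 72 minutes on placebo", so delta = -30 min among those who stay on treatment; SD s = 60; n = 150 per group; dropout d = 25 %; two-sided alpha 0.05; 90 % power. Assumptions not in the document: 60 min is also the SD of change, change is measured from baseline, and dropout splits by arm as stated below.

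**The plan's own figure.** Diluted effect 0.75 × 30 = 22.5 min. n = 2 × (1.960 + 1.282)² × 60² / 22.5² = 149.4, so 150 per group. This reproduces.

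**1. Equal random dropout, change scores, no placebo change.**
- Completers, 112.5 per group: estimate -30; SE = 60 × √(2/112.5) = 8.00; z = -3.75.
- Zero change: estimate (1-d) × delta = -22.5. With arm mean change m, the variance per arm is (1-d)s² + d(1-d)m². Melatonin: 0.75 × 3600 + 0.1875 × 900 = 2868.75. Placebo: 2700. SE = √((2868.75 + 2700)/150) = 6.09; z = -3.69.
- Ratio of z values: 3.69/3.75 = 0.98.

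The planned SE for the same 22.5 min effect was 60 × √(2/150) = 6.93. Counting the zeros as data gives 6.09, which corresponds to about 96 % power rather than 90 %.

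A placebo improvement loosens the match. With a placebo change of -30 min at 25 % dropout, the ratio is 0.93.

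**2. A difference created by dropout.** Parallel-arm simulation, 150 v 150, SD 60, no true effect, 25 % missing in each arm. On melatonin the chance of being missing rises with the child's change score (standardised change plus noise of equal size); on placebo dropout is random.

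| Common improvement | Completers reject | Zero change rejects |
|---|---|---|
| 0 min | about 66 % | about 65 % |
| 30 min | 67 % | 63 % |
| 40 min | 65-67 % | about 59 % |

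The completers' spurious difference is about -18 min; zero change reduces it to about 0.75 × 18 = 13.5 min, and the SE falls too.

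**3. Unequal random dropout, no true effect, improvement in both arms.** The rule creates a difference equal to the gap in missing shares times the common improvement. For 10 % v 25 %:
- 30 min: 0.15 × 30 = 4.5 min. Variances 0.9 × 3600 + 0.09 × 900 = 3321 and 2868.75; SE = √(6189.75/150) = 6.42; shift in z = 0.70; type I error about 11 %.
- 40 min: 0.15 × 40 = 6 min. Variances 3384 and 3000; SE = √(6384/150) = 6.52; shift in z = 0.92; type I error about 15 %.

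Simulations of this setting gave 9-15 %.

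**4. A selection model under which the check does better.** Suppose dropout on melatonin depends on final SOL rather than change, baseline-adjusted SOL is analysed, and missing SOL is set to baseline (baseline correlation 0.3 to 0.7, assumed). Zero change then agrees with a false completers' result in about 30-60 % of trials. Under step 2's model the agreement was about 86-99 %.

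**5. Model against check.** The aggregated analysis estimates the mean of individual treatment effects with within- and between-patient variance. The sensitivity analysis compares groups at each time point. Target, model and missing-data assumption all change at once.

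**The case against.** Several counter-arguments have force.

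- **It does not always repeat the completers' result.** A reader might infer from step 1 that the check nearly always confirms, whatever the missing children would have shown. The document does not support that. The near-identity needs change scores and similar dropout, and the article does not say whether change or SOL is analysed. Step 4 shows much lower agreement. With selective melatonin dropout at 25 % v 10 %, false rejection falls from about 70 % in completers to 62 %, 46 % or 30 % for placebo improvements of 0, 15 or 30 min. That is still far above 5 %, and the movement follows dropout rates and the common improvement rather than why children left.
- **The simulations are parallel-arm, while the section governs the crossover analysis.** This stands. A child who leaves loses later melatonin and placebo weeks alike, which makes similar missing shares plausible and 10 % v 25 % less so. A paired calculation (30 min effect, SD of differences 30 to 60, assumed) gives z ratios of 0.85 to 0.99 for 10-40 % dropout.
- **Completers are a stand-in.** The stated main approach is model-based, so step 2 illustrates the behaviour rather than predicting it.
- **The plan reads estimates and intervals, not only significance.** The fall from -30 to -22.5 min would be visible and matches the planning dilution. But the interval around it would be too narrow.
- **The article is condensed, and the analysis plan may add further checks.** That may be so. The point here is the rule the article does state, not what it leaves out.

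**Conclusion.** The concern holds in a limited form. The stated zero-change rule is a poor check on missing at random, for three reasons.

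1. It treats imputed values as observed.
2. With change scores and similar dropout it lets a dropout-made difference through almost unchanged, somewhat less so when both groups improve a lot. With unequal dropout and a common improvement it can create a difference of its own.
3. It changes the model together with the assumption, so a disagreement with the primary result could not be interpreted.

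The z ratio of 0.98 follows from the plan's own inputs, given 60 min as the SD of change, equal dropout and no placebo change. The rejection rates depend on assumed selection models and parallel-arm comparisons, and should be read as illustrations. Nothing here shows that the primary analysis is wrong or that dropout will distort it. The weakness lies in a supplementary analysis, but one that would be cited as evidence of robustness, so it should be changed.

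**What to change.** Replace the zero-change sentence in Missing data with a sensitivity analysis that keeps the aggregated multilevel model, and do the same with the first-period RCT model. Multiply impute missing SOL from that model under missing at random. Add a shift to the imputed SOL, separately for melatonin and placebo nights, over a stated range, for example 0 to 30 min, the upper end being the planned effect. Report the estimate and 95 % interval across the range, and the shift at which the interval includes zero.

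This informs judgement; it cannot prove whether dropout produced the effect. For example, an 18-min difference with SE 8 and 25 % missing on melatonin tips at about (18 - 1.96 × 8)/0.25 = 9 min, and would do so whether the 18 min were real or an artefact. What it gives the reader is a stated departure from missing at random whose plausibility can be argued.

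Cost: wording in the analysis plan and extra model runs. Multiple imputation is already foreseen for predictors and would be extended to the outcome. No new patients or data are needed. The downside is that results may look less robust than under the zero-change rule.

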#### Interim safety analysis

After 100 participants have been enrolled or after one year, whichever occurs first, the DSMB will supervise one interim analysis for safety only using treatment labels (A and B) without knowledge of the identity of each label to determine if there is an excess of adverse events in one group. A *p* value of 0.10 will be used as a decision criterion for stopping the study for harm. As no effectiveness endpoint will be evaluated, there will be no need to adjust the sample size.

#### Subgroup analyses

Primary subgroup analyses include the two main stratification factors: (1) age (<12, ≥ 12 years) and (2) country (Australia and Canada). Exploratory analyses will look at (3) the type of stimulant, (4) weight-adjusted dose of stimulant, (5) presence of psychiatric comorbid illness, (6) gender, (7) calendar time of enrollment as a proxy for differences by climactic season, (8) severity of SOL, and (9) referring physician/clinic.

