### Melatonin

First discovered in 1958 [20], melatonin is a hormone released by the pineal gland and regulates the sleep-wake cycle [28, 29], thermoregulatory cycle [30], reproductive rhythm [31], and immune function [32]. Its secretion follows a circadian rhythm that is entrained to the light/dark cycle and is regulated by the hypothalamic suprachiasmatic nucleus (the central pacemaker of the body) [28]. The secretion of melatonin is suppressed by daylight but increases with darkness; it regulates the circadian rhythm by promoting the desire to sleep at night [28]. Individuals with neurodevelopmental disorders often have biological clock or circadian rhythm disturbances, which result in sleep disorders [29]. Children with ADHD have a delayed endogenous circadian pacemaker as measured by delayed sleep onset, dim-light melatonin onset, and time of awakening [33–35]. These findings suggest that melatonin may be particularly effective in children with ADHD to help promote sleep onset by two possible routes: as a chronobiotic and as a hypnotic.

Classified as an NHP by Health Canada (HC), melatonin is available over the counter [36]. In Australia, melatonin may be obtained with a prescription or without, by ordering it through the internet. Melatonin is widely used in pediatric populations for the treatment of sleep disorders [37]. A 2003 survey of 671 US community-based pediatricians reported that approximately 25 % of physicians recommended melatonin for sleep problems in toddlers (1–8 %) and adolescents (15–19 %) [26]. A 2013 study conducted in Australia found that melatonin was prescribed 89.1 % of the time for poor sleep initiation in children by general pediatricians [27].

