### Study setting

The trial sites will be outpatient pediatric and/or family medicine clinics at hospital and community clinics in Australia and in Edmonton, Canada. Staff in all relevant clinics will be informed about the availability of the trial and will refer participants to the study investigators at each site. Community patients will also be able to be referred by their physician.

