### Randomization

Participants will undergo three pairs of treatment with melatonin and placebo. In each pair, the order of treatment will be randomized. In particular, the first period for each patient will be randomized in variable block sizes of 4 and 6, stratified by age (<12 and ≥ 12 years) and country (Canada or Australia), to ensure a balance of the treatment groups for the parallel-group RCT. The randomization code will be developed by the study statistician. The randomization code will be provided to the central research pharmacy for each participating site and to maintain the blind. When a participant has been enrolled, the research pharmacy will randomize the subject based on the master randomization list and courier six bottles numbered 1–6, corresponding to each week’s treatment. Each bottle will contain seven capsules (or 14 for children who weigh < 40 kg) to be taken over 7 days. Randomization codes will be kept by the research pharmacy in case the code needs to be broken for safety reasons as determined by the Data Safety and Monitoring Board (DSMB).

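### Enrollment date is the proxy for season, but Edmonton and Australia have opposite seasons, so a pooled calendar-time term attenuates a seasonal effect and could cancel or reverse it

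*Protocol article*

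**What the plan says.** The Subgroup analyses section names age and country as primary subgroup factors and then gives a second list, opening "Exploratory analyses will look at (3) the type of stimulant". Item (7) of that list is "calendar time of enrollment as a proxy for differences by climactic season". This states both the variable and its purpose.

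Study setting describes outpatient "clinics at hospital and community clinics in Australia and in Edmonton, Canada". Under Randomization, allocation in the first period is "stratified by age (<12 and ≥ 12 years) and country (Canada or Australia".

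The Aggregated analysis section explains how between-patient factors enter the multilevel model: "These terms describe the main effects of these factors, their interactions with the treatment, and their interaction with time". It mentions no interaction of a factor with country. No section converts enrollment date to local season, analyses it within country or crosses it with country. The expected split of participants between the countries is not given.

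**The concern.** A January enrollment is midwinter in Edmonton and midsummer in Australia. Across the pooled sample, calendar date therefore does not order children by season, which is the only purpose the protocol gives for the variable.

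The protocol's background gives some reason to look at season. It says of the hormone: "The secretion of melatonin is suppressed by daylight but increases with darkness". That sentence concerns the daily light cycle; extending it to season is an inference, though one that fits the investigators' decision to examine season.

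At stake is the reading of this one analysis. If melatonin worked differently in winter and summer, the two countries would pull the pooled term in opposite directions. A small estimate could then be taken as evidence of no seasonal difference when it reflects the coding.

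**Working it through.** **The plan's own figure.** The season analysis has no stated figure. The trial's sample size reproduces: a difference of 22.5 min, SD 60 min, two-sided alpha 0.05 and 90% power give 150 per group (power at 150 is 0.901), and 150/0.85 = 176.5, so 177 per group before the sleep-hygiene phase. None of this depends on the season variable.

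**Set-up.** Let c be Canada's share of participants. Let A_C and A_A be the winter-minus-summer differences in treatment effect in Canada and Australia, with enrollment even over the year. None of these values is in the protocol; all are assumptions. Dating by the northern calendar, the pooled contrast is

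c·A_C − (1−c)·A_A,

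and the average true seasonal contrast is c·A_C + (1−c)·A_A.

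**Case 1: equal amplitudes (A_C = A_A).** The retained fraction is |2c−1|. A simulation of the treatment-by-season interaction checked this with 300 participants, SD 60 min, a country main effect in the model and an assumed true seasonal difference of 30 min:

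| Share of larger country | Fraction kept | Difference recovered, calendar coding | Power, calendar coding |
|---|---|---|---|
| 50% | 0% | 0 min | 5% |
| 60% | 20% | 6 min | 8% |
| 70% | 40% | 12 min | 13% |
| 80% | 60% | 18 min | 25% |
| 90% | 80% | 24 min | 41% |

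Recoded to local season, the same data recover about 30 min with 57–59% power at every split. The country main effect was in the model throughout, so it does not restore the contrast. It shifts the level of the outcome in each country but still forces one calendar-by-treatment slope on both.

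**Case 2: effect proportional to day length.** Assume latitudes of about 53.5 N (Edmonton) and 27.5 S (the protocol says only Australia). Day length then runs from 7.2 to 16.8 h in Edmonton, a swing of 9.6 h, and from 10.3 to 13.7 h in Australia, a swing of 3.4 h. The two series have opposite phase but very different amplitude.

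- Cancellation: c × 9.6 = (1−c) × 3.4, so c = 3.4/13.0 = 26% (27% with unrounded swings).
- At 50:50: 0.5 × 9.6 − 0.5 × 3.4 = 3.1 h, against an average swing of 0.5 × 9.6 + 0.5 × 3.4 = 6.5 h. About 48% is kept.
- At c = 40%: 0.4 × 9.6 − 0.6 × 3.4 = 1.8 h against 0.4 × 9.6 + 0.6 × 3.4 = 5.88 h. About 31% is kept, and the sign is that of Canada, the smaller country.
- At c = 20%: 0.2 × 9.6 − 0.8 × 3.4 = −0.8 h. The sign is now Australia's, so the estimate is reversed if dates are read as northern seasons.

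The opposite sign is common to both cases. The loss, and the split at which it is complete, depend on amplitudes that the protocol does not give.

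**The case against.** The strongest objection is that item (7) is one entry in a list of nine factors and not a coding rule. It names a data source and a target, and assigning local season from a date and a site would be consistent with it. The derivation of an exploratory covariate is commonly left to the analysis plan, which is not shown. Part of this stands: the text does not forbid a local-season coding. But the protocol does state a variable, and across two hemispheres that variable does not measure what it is said to stand for. This is a stated choice that fits badly, not an absent detail, and an analysis plan that carried the words over would carry over the problem.

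A reader might also infer stronger conclusions, which the documents do not support:

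- *That a real seasonal effect cancels in the pooled analysis.* Full cancellation needs a particular combination of country split and amplitudes. The protocol gives neither.
- *That the pooled effect follows the larger country.* This holds under equal amplitudes. Under day-length scaling, it follows Canada from a share of about 26% upward, including splits where Canada is the smaller group.
- *That the seasonal question cannot be answered.* It can, because enrollment date and country together identify local season.
- *That the trial's main conclusions are at risk.* The primary aggregated analysis models a constant mean treatment effect, and the parallel-group analysis compares randomized first-period groups. Neither uses item (7).

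**Conclusion.** The point holds as a minor one. The stated proxy mixes opposite seasons when the countries are pooled. Using it as worded would attenuate a true season-by-treatment effect and could cancel or reverse it. Neither stratifying by country nor a country main effect corrects this.

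The size cannot be fixed from the protocol. Under equal amplitudes the loss is complete at 50:50, and 80% of the effect survives at 90:10. Under day-length scaling at the assumed latitudes, about half survives at 50:50 and the loss is complete near a 26% Canadian share. Whether season modifies the response to melatonin at all is unknown. Only this exploratory analysis is affected.

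**What to change.** Reword item (7) as local season at the site, in one of two ways:

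- day length at the site's latitude when the child starts the trial; or
- season by hemisphere, with Australian dates shifted by six months.

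Alternatively, keep calendar time but analyse it within country, or include a calendar-by-country-by-treatment term so that the seasonal effect can take a different sign in each country. Use raw calendar time in the pooled data only to look for a secular trend.

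The cost is one line of wording. Country is already a randomization stratum and item (7) itself needs the enrollment date, so no new data collection is required; the day-length version also needs each site's latitude. One small downside is that the six-month shift treats an Edmonton winter and an Australian winter as equal although their day-length swings differ; the day-length version avoids this. The definition is best settled before results are seen.
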